## Abstract

**Introduction:**

Studies suggest that access and exposure to green-blue spaces (GBS) have beneficial impacts on mental health. However, the evidence base is limited with respect to longitudinal studies. The main aim of this longitudinal, population-wide, record-linked natural experiment, is to model the daily lived experience by linking GBS accessibility indices, residential GBS exposure and health data; to enable quantification of the impact of GBS on well-being and common mental health disorders, for a national population.

**Methods and analysis:**

This research will estimate the impact of neighbourhood GBS access, GBS exposure and visits to GBS on the risk of common mental health conditions and the opportunity for promoting subjective well-being (SWB); both key priorities for public health. We will use a Geographic Information System (GIS) to create quarterly household GBS accessibility indices and GBS exposure using digital map and satellite data for 1.4 million homes in Wales, UK (2008–2018). We will link the GBS accessibility indices and GBS exposures to individual-level mental health outcomes for 1.7 million people with general practitioner (GP) data and data from the National Survey for Wales (n=~12 000) on well-being in the Secure Anonymised Information Linkage (SAIL) Databank. We will examine if these associations are modified by multiple sociophysical variables, migration and socioeconomic disadvantage. Subgroup analyses will examine associations by different types of GBS. This longitudinal study will be augmented by cross-sectional research using survey data on self-reported visits to GBS and SWB.

**Ethics and dissemination:**

All data will be anonymised and linked within the privacy protecting SAIL Databank. We will be using anonymised data and therefore we are exempt from National Research Ethics Committee (NREC). An Information Governance Review Panel (IGRP) application (Project ID: 0562) to link these data has been approved.

The research programme will be undertaken in close collaboration with public/patient involvement groups. A multistrategy programme of dissemination is planned with the academic community, policy-makers, practitioners and the public.

Strengths and limitations of this studyThis retrospective controlled evaluation of a natural experiment includes the majority of adults in Wales, UK between 2008 and 2018, minimising selection bias.Generating a national longitudinal dataset of changes in green-blue spaces (GBS) exposure and access to GBS for households will reduce ecological fallacy.Spatial and temporal accessibility data linked for individuals and their routinely captured health service use, together with potential confounders, will allow us to investigate the impact of GBS on well-being.Detailed self-report data on well-being and GBS visit behaviour from cross-sectional national survey data will be linked to health service utilisation data.Despite including a large number of potentially confounding variables, this non-randomised study using routinely recorded data may omit some unknown confounders, thereby introducing a moderate level of bias due to confounding.

## Introduction

Globally, 686 million people suffer with common mental health disorders (CMDs) such as depression or anxiety.^1^ In the UK, CMDs are experienced by around one in four of the population, and mental ill health costs the economy over £100 billion per annum in health, social care and quality of life loss costs.^2 3^ Subjective well-being (SWB) is also related to mental and physical health outcomes, including life expectancy,^4 5^ and is a key marker of quality of life.^6^ With increasing impacts on wider societal costs, CMDs and promoting SWB are growing in importance. Access to natural environments—considered here as ‘green-blue spaces’ (GBS)—such as parks and beaches—may provide opportunities to support and promote good public mental health and well-being.^7 8^ The evidence base on the impacts of GBS, on mental health and well-being is growing rapidly. Current research suggests that the benefits may differ by population group, context and health outcome.^9 10^

Recent systematic reviews, of predominantly cross-sectional studies, indicate positive relationships between mental health and SWB outcomes with living near GBS.^11 12^ Access to GBS is positively associated with GBS use, and using GBS may improve health outcomes through a number of mechanisms. For example, increased physical activity,^13 14^ psychological restoration,^15 16^ noise mitigation,^17^ heat and humidity regulation,^18 19^ increased social interaction and cohesion.^20–22^ Contrary to these findings, a study in New Zealand found no evidence that GBS influenced cardiovascular disease mortality^23^ and suggested that GBS and health relationships may vary according to country or environmental contexts.

Many studies have found that access to GBS can vary across socioeconomic status (SES) areas; with more deprived areas tending to have poorer access to GBS.^24 25^ Differences in the distribution of GBS across SES may influence and contribute to SES-related health inequalities.^26^ Furthermore, individuals from higher SES groups are more likely to select living in greener neighbourhoods.^27^ Previous studies lack censoring for births, deaths and migration, which may have led to health selection effects which can alter the strength of association. There is also a lack of large-scale population-level studies which have systematically and explicitly examined associations within and between subgroups other than SES^10^ (eg, by gender,^28–30^ age, education^22 31^). Furthermore, ethnic minority groups are under-represented in studies due to selective non-response.^32^ Studies that have focused on differences between ethnic minorities found positive effects of GBS on well-being differed by ethnicity^33^ and ethnic minorities had poorer access to GBS.^34^

Study methods used to define access to GBS differ; some studies have calculated small area-level metrics and others have used distances. There is no accepted method to define GBS or for measuring different types of GBS (eg, according to general land cover categories, ecosystems or landscape classifications).^35–41^ However, it is difficult to expect an authoritative voice on defining GBS access because how people engage with GBS varies by population subgroup and environmental context. Therefore, how GBS is defined will vary by study design and the focus of the research. We propose to take an approach that will consider land use but also access points, rights of way and amenities such as benches. There are also differences in study aims because of differing perspectives; such as health research, environmental research and policy. Few studies have also considered the issue of access to blue spaces,^42 43^ which has also contributed to diversity in GBS accessibility measures. Although there is now a significant body of research, there are few longitudinal studies on mental health outcomes in response to changes in GBS access or with assessments of actual visits to GBS.^44–47^

We define GBS accessibility indices as metrics that represent how people may access GBS (figure 1). GBS exposure is the ambient environment that people experience because of where they live and will be defined as greenness immediately surrounding home/can be seen out of the window. By including both of these measures in our study, we will be able to build a more holistic view of how GBS impacts CMD and well-being.

**Figure 1 F1:**
[figure not shown]
Residential GBS access for each home. (1) Network buffer defines household access boundary (eg, 10 min walk). (2) GBS A and B included in access estimates including access points, rights of way and facilities such as benches (GBS C excluded). (3) Access measures include GBS quality, size, function and weighted network distances (d_i_) to access points. (4) Longitudinal exposure estimates created through quarterly repeat analysis. (5) GBS, green-blue spaces.

### Aim

Our primary aim is to quantify the impact of changes in access to GBS and ambient GBS exposure on CMD and SWB, for a national population. This will be fulfilled through a number of objectives within two work packages (WPs). WP1 will use routinely collected health and demographic data (data collected for purposes other than research^48^) stored in an anonymised databank to examine the risk of CMD using longitudinal changes in access to neighbourhood GBS. WP2 will link routine data in the anonymised databank with in-depth survey responses from the data linked National Survey for Wales (NSW) to evaluate a representative sample of Welsh residents’ self-reported well-being and GBS use.

### Objectives

#### WP1

Create a longitudinal dataset of GBS in Wales using UK Ordnance Survey (OS), local authority and remotely sensed satellite data.Create longitudinal, residential GBS accessibility indices for all homes in Wales using the longitudinal GBS dataset in a Geographic Information System (GIS).Create an 11-year dynamic cohort of individual-level longitudinal residential GBS accessibility indices to answer the research question(s): ‘Do people with different GBS access through time have different associated risks of having a CMD?’ and ‘Is the association between changes in access and exposure to GBS and CMD modified by multiple sociophysical variables, migration and socioeconomic disadvantage?’

### WP2

Create data linkages between survey and routinely collected data within the Secure Anonymised Information Linkage (SAIL) for household-level GBS accessibility indices, and individual-level health and demographic data.Complement residential GBS accessibility indices by including GBS usage from the data-linked NSW to model interactions to answer research question: ‘Are there associations between residential GBS access and exposure, and well-being and CMDs? Are these associations modified by GBS use and multiple sociophysical modifiers?’We will consider stratifying by CMD to check for reverse causation.

## Methods and analysis

### Design

The GBS project is a retrospective and controlled, population-wide study. We will evaluate the association between changes in access and exposure to GBS, on the risk of CMD (WP1) and SWB (WP2). This could be either at environment level (eg, a change in the GBS itself) or person level (eg, moving home, better access to transport). WP1 will use longitudinal data to examine variability in time and space of access and exposure to GBS and examine whether this could be due to planning and environmental policies. WP2 will use cross-sectional data to investigate whether visits to GBS improve SWB.

### Participants

Our study population contains people aged 16 years and older living in Wales, UK. WP1 includes the total adult population registered with a general practitioner (GP), providing GP records to SAIL. This is expected to be about 1.7 million adults in Wales (see figure 2). WP2 includes a representative sample of the adult population in Wales based on the NSW for 2 years (cross-sectional samples in 2016/2017 and 2017/2018). The NSW has an annual sample of approximately 12 000 responders and GBS visit questions are asked of 50% of that sample. This provides a total cross-sectional sample of 12 000 (over the 2 years) for this part of the study.

**Figure 2 F2:**
[figure not shown]
Flow diagram of proposed number (1.7 million adults) we currently have before exposure group allocation. GBS, green-blue spaces; GP, general practitioner.

### Research environment

We will use a secure GIS platform hosted by United Kingdom Secure e-Research Platform (UKSeRP).^49^ High-resolution map data from the OS are stored in the GIS, including point data for all residences (AddressBase Premium), and road network data.^50 51^ Environment data will be collected, stored and processed to generate household - level GBS accessibility indices.

In parallel with, but separate from the GIS, is the SAIL databank.^52–54^ Data linkage completed at our Trusted Third Party, will enable a longitudinal cohort to be created before statistical analysis is conducted within SAIL. The SAIL Databank contains longitudinal health, social and education data formore than 5 million people, which includes the current population of Wales, UK (3.1 million people) at any one time. The databank includes over 15 billion anonymised records and was designed to overcome data sharing issues.

A strength of the SAIL platform is the method for anonymising all individuals and households in Wales. Data are anonymised through the split file process.^52 53^ Whereby the dataset is separated into identifiable (eg, address) and non-identifiable (GBS access and exposure) components. The identifiable component is transported to our trusted third party (TTP), NHS Wales Informatics Service.^55^ The non-identifiable component is sent securely to the SAIL Databank. The TTP anonymise and encrypt the identifiable data and each individual record is assigned a unique linking field. An Anonymised Linking Field (ALF) is assigned to individuallevel data and a Residential Anonymised Linking Field is assigned to a place of residence.^55^ The anonymised elements of the dataset are then sent to SAIL to be loaded. These elements are then recombined with the non-identifiable (GBS access and exposure) component of the dataset, which makes them ready for linkage with other datasets in the SAIL Databank (see figure 3).

**Figure 3 F3:**
[figure not shown]
Diagram of proposed GIS data preparation and data linkage in SAIL databank. GBS accessibility and exposure indices created within a secure GIS platform will be linked at household level with demographics from Welsh Demographic Service (WDS) and National Survey for Wales (NSW). Common mental health conditions from GP records will be linked at individual level with the NSW and WDS. Linkage will be undertaken by our TTP (NHS Wales Informatics Service). ABP, AddressBase Premium; ALF, Anonymised Linking Field; GBS, green-blue spaces; GP, general practitioner; GIS, Geographic Information System; NDVI, Normalised Difference Vegetation Index; ONS, Office for National Statistics; OS, Ordnance Survey; RALF, Residential Anonymised Linking Field; SAIL, Secure Anonymised Information Linkage; TTP, Trusted Third Party; WDS, Welsh Demographic Service; WLGP, Welsh Longitudinal General Practice; WP1, work package.

### Data sources

#### Environment datasets

We will create a longitudinal, national dataset of GBS for Wales (2008–2018) using temporally and spatially referenced satellite imagery.^56^ We will also develop a typology of GBS and collate data from multiple sources to augment the all-Wales OS data we hold in our GIS database (OS Mastermap).^50 51 57^ Using satellite imagery, we will extract temporal trends of ‘greenness’ (using measures such as the Normalised Difference Vegetation Index (NDVI), which has been used in previous studies^58^) for every household in Wales and we will also explore the integration of new GBS and land use data as they become available and are published (eg, OS Greenspace data^59^) and local authority audits of GBS.

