### GBS accessibility and exposure dataset

There is no clear consensus in the existing literature on the most appropriate measures of GBS access and/or exposure.^42^ Using the aforementioned environment datasets, this project will collate a set of measures using criteria including longitudinal consistency, spatial resolution and evidence for associations with mental health and SWB outcomes. We will create residential-level exposure measures by modelling the ambient home environment, that is, the GBS immediately surrounding their home and what they see out of their window. This metric will include measures such as greenness (NDVI), urban trees and garden size. The access measures will represent people’s potential to visit GBS in their locality. We will adapt a previous methodology that modelled ‘change in alcohol outlet density and alcohol-related harm to population health’ (CHALICE).^60^ The distance decay for this accessibility model will be updated to emulate how people engage with GBS as opposed to alcohol outlets. People will behave differently in accessing GBS, compared with how they may access alcohol outlets. For example, people may be prepared to walk or drive further to access some green blue spaces compared with alcohol outlets.^61^ Our modelling will consider differential associations for key subgroups (eg, deprived populations) thereby minimising risks that recommendations could increase inequalities. We will create a number of accessibility and exposure measures, allowing planners to consider the configuration (size, function, quality) of the most beneficial mix of spaces. We will also measure, for each adult, change in GBS access and exposure for the study period. Again, we will build on the CHALICE study^62^ that measured change in alcohol outlet density by calculating change in density between the current and previous quarter and also the change between each quarter and baseline.

The longitudinal, household-level, GBS accessibility and exposure dataset will be imported into the SAIL databank and linked with health datasets that are held within the SAIL Databank. Household identifiers (Unique Property Reference Numbers, UPRNs) will be used to distinguish each household in the GIS and will have attached to each a GBS accessibility and exposure index (see figure 3). Household identifiers will be replaced with a Residential Anonymised Linking Field within SAIL.^63^

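### The green-blue space (GBS) layer is described as covering Wales with no extension into England, so network-based access would be understated for homes whose catchment crosses the border

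*Protocol article*

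**What the plan says.** Three parts of the protocol article bear on this point.

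- **How access is defined.** The Figure 1 caption says "Network buffer defines household access boundary (eg, 10 min walk"), and that "Access measures include GBS quality, size, function and weighted network distances" to access points. The section on the GBS accessibility and exposure dataset says the distance decay borrowed from an earlier alcohol-outlet study will be updated, because "people may be prepared to walk or drive further to access some green blue spaces compared with alcohol outlets". None of these rules mentions a national boundary.
- **What the GBS layer covers.** The first WP1 objective is "Create a longitudinal dataset of GBS in Wales using UK Ordnance Survey (OS), local authority and remotely sensed satellite data". Environment datasets states "We will create a longitudinal, national dataset of GBS for Wales (2008–2018) using temporally and spatially referenced satellite imagery", and that the project will also "collate data from multiple sources to augment the all-Wales OS data we hold in our GIS database". Table 1 gives Wales as the coverage of the GBS accessibility and exposure dataset.
- **Which homes are scored, and how change arises.** The second WP1 objective derives indices from this dataset for every home in Wales. The Design section counts moving home as a person-level change in access. Change is measured from quarter to quarter and against baseline. Table 2 lists access and exposure as primary exposures in both work packages, and time of move(s) as a secondary exposure and interaction term in WP1.

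**The concern.** The access rule follows the road and path network outward from the home and takes no account of a border. The layer it draws on is described as Welsh. For a home close to England these do not match: a park on the English side can lie inside the home's catchment and still be absent from the layer.

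If so, the shortfall depends on where the home is, so it is not random error. None of the confounders listed in Table 2 (deprivation, settlement type, gender, age, comorbidities and, in WP2, education, marital status and visits) represents proximity to the border. WP2 is cross-sectional and uses the level of access, so the understatement enters directly. In WP1, a person who moves between a border home and an inland home would be recorded as gaining or losing access even if the true access were the same at both. Moves are a named source of exposure change and a named interaction.

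**Working it through.** The article gives no figure for this point, so there is nothing to reproduce. The calculation below shows only how large the shortfall at a single home could be.

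**Inputs.** From the article: a network buffer with a 10-minute walk as the example, and distance weighting (Figure 1 and the accessibility dataset section). Not in the article: the final buffer radius, the decay function, and the number of homes near the border. Assumptions: a straight border, a circular catchment in place of a network one, uniform GBS density, and no GBS data beyond the border.

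**Fixed buffer.** With radius R, a home at distance d from the border and x = d/R, the share of the catchment cut off is

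lost = [arccos(x) − x·√(1 − x²)] / π

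- x = 0: 1.571 / π = 0.50
- x = 0.25: (1.318 − 0.242) / π = 0.34
- x = 0.5: (1.047 − 0.433) / π = 0.20
- x = 0.75: (0.723 − 0.496) / π = 0.07
- x ≥ 1: 0

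**Exponential distance decay.** With weight exp(−r/L) and u = d/L, the lost share is

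lost = (1/π) ∫ (1 + u/cos θ)·exp(−u/cos θ) dθ, for θ from 0 to π/2

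This gives 0.50, 0.42, 0.35, 0.24, 0.10 and 0.04 at u = 0, 0.25, 0.5, 1, 2 and 3. The loss fades with distance from the border but has no sharp edge.

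**Movers.** Suppose two homes have the same true index A, one at half the buffer radius from the border and one inland. They are scored 0.80A and A. A move inland then shows a gain of 0.20A, and the reverse move a loss of 0.20A. From a home on the border itself the false gain is 0.50A. A move between two homes equally close to the border adds little, because both are understated by a similar amount.

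**People who stay.** Write the true additive index as W + E, the Welsh and English parts. The scored index is W. The true change is (W_t − W_0) + (E_t − E_0), and the scored change is W_t − W_0. If E is constant, the omission cancels. Only a real change on the English side is missed.

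**Ambient exposure.** Greenness, urban trees and garden size describe the immediate surroundings of the home. Very little of that area can lie across the border, so these measures are largely untouched.

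**The case against.** The strongest reply is that the article never says any layer is cut at the border. To say that the OS holding covers all of Wales does not say that it ends there. The plan is also to "collate data from multiple sources", whose extent is not stated, and no extent is given for the satellite imagery or the road network. Table 1's entry of Wales may describe the homes indexed, not the spaces allowed to count towards them. A processing margin is the kind of GIS detail that a condensed article may leave to a fuller document. No driving catchment is specified either: the remark about driving only explains why the borrowed distance decay needs changing.

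Most of this stands. A reader might infer that the data definitely stop at the border and that border homes will certainly be scored too low; the documents do not establish that. A reader might also infer serious bias in the national estimates. The article gives neither the radius nor the share of homes affected, so no such bias can be computed, and the only buffer it mentions is short.

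The reply does not remove the point. The objectives define the layer as GBS in Wales and then derive every home's index from that layer. Followed as written, this leaves out English spaces that the access rule would count. The further sources serve a dataset that is itself described as being for Wales, so they do not by themselves imply cross-border data.

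**Conclusion.** The point holds conditionally. If the dataset is built as described, network-based access is understated for homes whose catchment reaches into England, and moves between border and inland homes carry false change. At a single home the loss runs from 50% on the border to 20% at half the buffer radius and zero at one radius or more, under the geometric assumptions above.

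The effect is confined to the access indices. It largely cancels in the change measures of people who do not move, and it probably concerns few homes under a 10-minute-walk buffer. A longer catchment would widen the strip affected, but the article fixes none. The effect on the national estimate is unknown. This is a low-cost improvement to part of the primary exposure, not a flaw that undermines the study.

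**What to change.** Extract the map, road-network and satellite layers for Wales plus a margin into England at least as wide as the largest network distance used in any access index, and state this in the description of the environment datasets. Where comparable data cannot be had on the English side, flag homes whose catchment crosses the border and repeat the WP1 and WP2 access models without them as a sensitivity analysis.

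The margin is best settled when the data are acquired, before quarterly indices are computed for the 1.4 million homes. A later analysis can exclude border homes but cannot restore the missing spaces. The cost is a wider extract and one repeat of the access models. The downside is that indices near the border may lack local authority audit data and rest on map and satellite sources alone.
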